## Abstract

**Background:**

Insomnia and eveningness are common and often comorbid conditions in youths. While cognitive behavioural therapy for insomnia (CBT-I) has been suggested as a promising intervention, it remains unclear whether it is sufficient to also address circadian issues in youths. In addition, despite that light has been shown to be effective in phase-shifting one’s circadian rhythm, there has been limited data on the effects of bright light therapy and its combination with CBT-I on sleep and circadian outcomes in youths. The current protocol outlines a randomised controlled trial that examines the efficacy of CBT-I and CBT-I plus bright light therapy (BLT) in reducing insomnia severity, improving mood symptoms and daytime functioning (e.g. sleepiness, fatigue, cognitive function), and improving subjective and objective sleep and circadian measures compared to a waitlist control group.

**Methods:**

We will carry out a randomised controlled trial (RCT) with 150 youths aged 12–24 who meet the criteria of insomnia and eveningness. Participants will be randomised into one of three groups: CBT-I with bright light therapy, CBT-I with placebo light, and waitlist control. Six sessions of CBT-I will be delivered in a group format, while participants will be currently asked to use a portable light device for 30 min daily immediately after awakening throughout the intervention period for bright light therapy. The CBT-I with light therapy group will receive bright constant green light (506 lx) while the CBT-I with placebo light group will receive the modified light device with the LEDs emitting less than 10 lx. All participants will be assessed at baseline and post-treatment, while the two active treatment groups will be additionally followed up at 1 month and 6 months post-intervention. The primary outcome will be insomnia severity, as measured by the Insomnia Severity Index. Secondary outcomes include self-reported mood, circadian, daytime functioning, and quality of life measures, as well as sleep parameters derived from actigraphy and sleep diary and neurocognitive assessments. Objective measures of the circadian phase using dim-light melatonin onset assessment and sleep parameters using polysomnography will also be included as the secondary outcomes.

**Discussion:**

This study will be the first RCT to directly compare the effects of CBT-I and BLT in youths with insomnia and eveningness. Findings from the study will provide evidence to inform the clinical management of insomnia problems and eveningness in youths.

**Trial registration:**

ClinicalTrials.gov NCT04256915. Registered on 5 February 2020.

**Supplementary Information:**

The online version contains supplementary material available at 10.1186/s13063-024-08090-0.

## Introduction

### Background

#### Insomnia and eveningness in youth

Insomnia is the most common sleep complaint in youths, with a prevalence rate of 7.8–23.8% for insomnia disorder [1–6] and up to 40% for insomnia symptoms [2]. Youth insomnia tends to run a chronic course and persist into adulthood [7, 8]. Fernandez-Mendoza and colleagues followed a group of children (*n* = 502, median age of 9 at baseline) for 15 years and found that children with insomnia symptoms continued to have sleep problems in adolescence (~ 54%; median age, 16) and young adulthood (~ 62%; median age, 24), respectively [8]. If left untreated, insomnia may be associated with long-term adverse outcomes, such as an increased risk for physical and mental health problems [9], incidences of substance use [6], impaired daytime functioning, and increased school absenteeism [10].

Another significant change during adolescence is a gradual shift in circadian preference towards eveningness. This increased evening preference is intrinsically associated with pubertal development [11, 12], during which peak eveningness is reached at the end of adolescence [13]. Eveningness in youths is often associated with a constellation of adverse outcomes, including an increased risk for physical [14], mental [15–17], and sleep problems [18]. It is also frequently implicated in insomnia symptoms in adolescents, with those having an eveningness tendency having up to a 2.5-fold risk of insomnia problems. Existing research suggested that eveningness is a unique contributing factor to insomnia in adolescents, where a misaligned circadian rhythm potentially contributes to the aetiology of insomnia and implicates the phenomenology of insomnia, particularly with sleep-onset insomnia [19, 20]. Moreover, increasing research has demonstrated the potential synergistic effects of eveningness and insomnia on daytime sleepiness and mental health outcomes, such as depressive and anxiety symptoms. Previous studies showed that adolescents with both eveningness and insomnia were 1.3–4.9 times more likely (compared to insomnia alone) and 2.8–6.9 times more likely (compared to eveningness alone) to develop mental health problems [17, 21]. While both insomnia and eveningness are linked to a wide range of adverse outcomes in youths, the research on the treatment for this vulnerable group has been limited to date. The intricate relationship between insomnia and eveningness and their associated consequences underscore the need for concurrently addressing sleep and circadian issues in youths.

#### Treatment for youth insomnia

Although cognitive behavioural therapy for insomnia (CBT-I) is recommended as the first-line treatment for insomnia in adults with substantial empirical support [22, 23], research on the efficacy of CBT-I in adolescents has been limited. Åslund et al. (2018) conducted a meta-analysis on the effect of CBT-I in school-age children and adolescents and found only six RCTs (528 pooled samples, mean age 14.6 years) which showed a small-to-large magnitude of improvements in sleep parameters, specifically in sleep onset latency (SOL) [24]. Another meta-analysis by Blake et al. (2017) on adolescent cognitive behavioural sleep interventions included 9 trials (357 pooled samples, mean age 15.0 years) and found that cognitive and behavioural interventions improved not only various subjectively and objectively measured sleep parameters, but also daytime sleepiness, depression, and anxiety severity [25]. Despite some findings supporting the efficacy of CBT-I in youths, it was observed that up to 25–40% of young people treated with CBT-I showed minimal treatment response or failed to achieve a remission [26], suggesting the need to consider and/or integrate alternative strategies to enhance treatment outcomes.

The Transdiagnostic Sleep and Circadian Intervention (TranS-C) is a programme that combined conventional therapeutic components from CBT-I with additional circadian-related components to address both sleep and circadian disturbances [27]. A series of studies have provided support for the TranS-C programme as a promising intervention for improving sleep and advancing the circadian phase in youths [28–30]. Specifically, in a study comparing the efficacy of TranS-C versus psychoeducation in 176 youths aged 10 to 18, TranS-C was found to result in significantly greater improvements in self-reported sleep and circadian measures at post-intervention [28]. In addition to the cognitive-behavioural approach, the use of chronobiotics has gained increasing attention as a therapeutic approach in recent years. Light is the most potent zeitgeber that entrains the endogenous circadian clock to the surrounding environment. Under controlled laboratory conditions, light has been shown to be effective in shifting the human circadian rhythm and subsequently used as a therapeutic intervention [31, 32]. In adults, bright light therapy (BLT) has been shown to improve circadian outcomes, insomnia symptoms, and depressive symptoms [33, 34]. However, the evidence of BLT in the youth population remains relatively limited. A study conducted by Gradisar et al. (2011) in adolescents with delayed sleep phase disorder, a clinical sleep disorder reflecting the extreme end of eveningness, showed moderate to large effects of CBT-I with adjunctive BLT in reducing sleep onset latency (*d* = 0.65–1.13), advancing bedtime and rise time (*d* = 0.89–1.24), and improving daytime functioning (*d* = 0.75–0.79) [35]. Nonetheless, previous research utilising light therapy in adolescents was mainly conducted in either mixed clinical samples [36] or those with delayed sleep phase disorder [35, 37]. It remains unclear how to address circadian issues in the context of youth insomnia, specifically whether CBT-I alone is sufficient to tackle eveningness in youths diagnosed with insomnia or if an adjunctive circadian-focused intervention, i.e. bright light therapy, could additionally address the circadian components of youth insomnia, thereby enhancing the treatment outcomes.

### Study objectives

Given the gap in the current literature and the need to address circadian-related factors in youths with insomnia, this study aims to examine the efficacy of CBT-I and CBT-I plus bright light therapy in reducing insomnia severity in adolescents compared with a waitlist control. The secondary aim of the study is to examine the effects of CBT-I and CBT-I plus bright light therapy on mood symptoms and daytime functioning (e.g. sleepiness, fatigue, cognitive performance), as well as subjective and objective sleep and circadian measures.

The primary hypotheses for the trial are as follows:Both CBT-I and CBT-I plus BLT will lead to an improvement in self-reported insomnia symptoms by the end of treatment as compared to the waitlist control.CBT-I plus BLT will additionally lead to an advancement of chronotype and sleep onset by the end of treatment compared to the waitlist control.Changes in insomnia will mediate the changes in mood and other daytime symptoms.

The secondary hypotheses are as follows:CBT-I and CBT-I plus BLT will improve objectively measured sleep outcomes, mood symptoms, daytime functioning, and insomnia-related behaviours and cognitions by the end of treatment compared to the waitlist control.The treatment effects of CBT-I and CBT-I plus BLT will be maintained over time at 1 month and 6 months after treatment.

## Methods

### Trial design and setting

This study is a randomised, assessor-blind, parallel-group, controlled trial with three arms. The trial will be conducted across two centres in Hong Kong: The Sleep Research Clinic and Laboratory at the Department of Psychology of the University of Hong Kong and the Department of Psychiatry at the Chinese University of Hong Kong. Youths who meet the study criteria will be randomly assigned to one of the three groups: CBT-I with adjunctive bright light therapy (CBTI + BLT), CBT-I with placebo light therapy (CBTI-BLT), or waitlist control (WL). The study protocol was approved by the Human Research Ethics Committee at The University of Hong Kong (Ref: EA1802063) and the Joint CUHK-NTEC Clinical Research Ethics Committee (Ref: 2019.339). The present protocol used the SPIRIT reporting guidelines [38] (The SPIRIT Checklist can be viewed in supplementary file 1).

### Participants

Participants aged 12–24 years will be recruited from the community, local schools, universities, and hospitals via social media promotion, flyers, mass emails, and invitation letters sent to all relevant institutions in Hong Kong. This age range was chosen to reflect the puberty onset and a wider span of adolescence till the early phase of young adulthood, where sleep and circadian issues continue to be prevalent [13]. The inclusion criteria are as follows: (1) having a chief complaint of difficulty initiating sleep at least three times a week for 3 months or more, with clinically significant impairment or distress, (2) scored ≥ 9 on the Insomnia Severity Index (ISI) [39], a suggested cut-off for clinical insomnia in youths [40], (3) scored ≤ 11 on the reduced Morningness-Eveningness Questionnaire (rMEQ) [41], the conventional cut-off for classifying evening type, (4) having a sleep onset time at or later than 23:15 (for those aged 12), 23:30 (for those aged 13–14), or 00:00 (for those aged 15 or above) for at least three nights per week, as confirmed by a prospective 7-day sleep diary. Participants will be excluded if they meet the following exclusion criteria: (1) having a current diagnosis or a history of manic or hypomanic episodes, schizophrenia spectrum disorders, neurodevelopmental disorders, organic mental disorders, intellectual disabilities, or substance abuse or dependence, (2) having a prominent medical condition known to interfere with sleep continuity and quality (e.g. eczema, gastro-oesophageal reflux disease), (3) having a clinically diagnosed sleep disorder that may disrupt sleep continuity and quality (e.g. narcolepsy, sleep-disordered breathing, restless leg syndrome) except for insomnia disorder and delayed sleep–wake phase disorder, (4) concurrent and regular use of medications known to affect sleep continuity and quality (e.g. hypnotics), (5) initiation or change of medications that could interfere with the circadian rhythm (e.g. lithium, melatonin supplements, melatonin agonist) within the past 3 months, (6) presence of clinically significant suicidal ideation with a plan or an attempt, (7) concurrently receiving any forms of structured psychotherapy, (8) presence of hearing or speech deficit or eye disease (e.g. retinal blindness, severe cataract), (9) being a night shift worker, and (10) had trans-meridian flight in the past 3 months or during the study.

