### Procedures

Interested individuals can register for the study using an online application form and will be initially screened based on age, ISI score ≥ 9, and rMEQ score ≤ 11. Potential eligible individuals will then be invited to attend a face-to-face clinical interview to ascertain their eligibility for the trial. The diagnoses of sleep disorders and psychiatric disorders will be ascertained using the Diagnostic Interview for Sleep Patterns and Disorders [42] and the Mini International Neuropsychological Interview, respectively [43]. After confirming their eligibility, participants will be randomised to one of the following groups: CBTI + BLT, CBTI-BLT, and WL. Assessments are scheduled at pre-treatment (Week 0), during treatment (Week 2 and Week 4), and post-treatment (Week 7). Assessments at Week 2 and Week 4 will consist of two self-report measures (Insomnia Severity Index and Hospital Anxiety and Depression Scale) for monitoring the clinical status of the participants. Actigraphy will also be used in Week 4 to objectively monitor sleep and circadian-related changes and light exposure across the groups. The two active intervention arms (CBTI + BLT and CBTI-BLT) will be additionally followed up at 1 month and 6 months after the conclusion of the last group session. Participants in the WL group will be offered the treatment (either CBTI + BLT or CBTI-BLT) after completing the post-wait assessment. Figure 1 shows the study flowchart, and the study schedule is summarised in Table 1. Participants will receive HKD 500 (~ USD 64) at the end of the follow-up period as a token of appreciation of their participation in this trial.

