#### Main analysis

The main analyses will be conducted following the intention-to-treat principle. Multilevel modelling (MLM) with restricted maximum likelihood estimation and an unstructured variance–covariance matrix will be used to analyse the main hypotheses on outcome measures. The use of MLM in analysing RCT data has the advantage of accounting for individual differences as a random effect [67–69]. MLM also has advantages over the traditional general linear model approach (e.g. mixed model repeated measures ANOVA) as it is unaffected by randomly missing data and can handle both time-dependent and independent covariates [67, 69]. Missing data for dependent variables will be assumed to be missing at random and accounted for by the maximum likelihood estimation. Two sets of MLMs will be conducted; one will include three treatment arms (CBTI + BLT vs CBTI-BLT vs WL) and two timepoints (pre-treatment vs post-treatment) as fixed effects; the second set will consist of two treatment arms (CBTI + BLT vs CBTI-BLT) and four timepoints (pre-treatment vs post-treatment vs 1-month follow-up vs 6-month follow-up) as fixed effects. The treatment × time interaction will also be included as a fixed effect on both MLMs and will be considered the treatment effect, while repeated measures will be nested within individual participants as random intercepts. A *p*-value of 0.05 represents statistical significance in all analyses. The *p*-values on outcome measures will be adjusted using the Benjamini–Hochberg procedure with a false discovery rate set as 20% to account for multiple comparisons.

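### Exclusion criterion 10 extends to flights taken during the study, so as written it excludes randomised participants and conflicts with the intention-to-treat analysis

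*Protocol article*

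**What the plan says.** Participants (protocol article) introduces ten criteria with "Participants will be excluded if they meet the following exclusion criteria". The tenth applies to those who "had trans-meridian flight in the past 3 months or during the study".

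Procedures gives the order of events: "After confirming their eligibility, participants will be randomised to one of the following groups: CBTI + BLT, CBTI-BLT, and WL". All arms are assessed from Week 0 to a post-treatment visit at Week 7. The active arms alone "will be additionally followed up at 1 month and 6 months after the conclusion of the last group session". For the waitlist, "Participants in the WL group will be offered the treatment (either CBTI + BLT or CBTI-BLT) after completing the post-wait assessment"; the study schedule (Table 1) shows no later waitlist assessment.

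Main analysis states: "The main analyses will be conducted following the intention-to-treat principle". It plans two sets of multilevel models. One has three arms and two timepoints (pre- and post-treatment). The other has the two active arms and four timepoints, up to 6 months. Missing outcomes are assumed missing at random and handled by maximum likelihood.

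**The concern.** An exclusion criterion should rest on what is known when a participant enters the trial. A flight taken during treatment or follow-up is not known then. If it leads to exclusion, a randomised person leaves because of something that happened after allocation, and the analysed groups are no longer the groups that randomisation formed. That is what an intention-to-treat analysis is meant to prevent.

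Two things are at stake. One is which participants count in the Week 7 comparison of insomnia severity, on which the first primary hypothesis rests. The other is how many randomised participants remain in the 6-month analysis of whether effects are maintained. The article does not define when the study ends for this rule, nor what happens to the data of someone who flies.

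**Working it through.** **1. The passages side by side.**
- Eligibility is confirmed, and randomisation follows (Procedures).
- Criterion 10 covers the past 3 months and also the study period (Participants). The first part can be checked at entry. The second part is mostly after randomisation.
- Criterion 5, the parallel criterion on drugs that affect circadian rhythm, stops at the past 3 months. Only criterion 10 goes on into the study.
- The wording is in the past tense and does not mention planned or expected travel.
- The main analyses follow intention-to-treat (Main analysis).

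Taken literally, the second part of criterion 10 and the analysis principle cannot both be followed for a randomised participant who flies.

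**2. The plan's own figures.** The article gives no number for flight exclusions, so there is none to reproduce. The arm size used below is from Sample size estimation: 111 × 1.3 = 144.3, stated as 144, or 48 per arm. There is little room for further loss. With the anticipated 30% attrition, 144 × 0.7 = 100.8, already below 111.

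**3. Exposure windows.** The waitlist window is 7 weeks. For the active arms it is the week of the last session plus 6 months (365.25 / 2 / 7 = 26.1 weeks). With six weekly sessions and a Week 7 assessment, I assume that the last session falls between Week 5 and Week 7.

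| Last session | Active window (weeks) | Ratio to 7 weeks |
|---|---|---|
| Week 5 | 31.1 | 4.4 |
| Week 6 | 32.1 | 4.6 |
| Week 7 | 33.1 | 4.7 |

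Up to Week 7 the window is 7 weeks in every arm, a ratio of 1.0.

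**4. What each planned model sees.**
- Three arms, pre- and post-treatment: equal windows. If travel and its detection are alike across arms, expected exclusions are equal.
- Two active arms to 6 months: the same window in both, so schedule length creates no imbalance between them. The concern is depletion.

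**5. Illustration of size.** The flight rate is an assumption. Let r be the risk of at least one trans-meridian flight in 7 weeks, with a constant hazard. The risk over T weeks is then 1 − (1 − r)^(T/7). With T = 32.1 and 48 per arm:

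| Assumed r | Flyers of 48 by Week 7, any arm | Flyers of 48 by 6-month visit, each active arm |
|---|---|---|
| 2% | 1.0 | 4.2 |
| 5% | 2.4 | 10.1 |
| 10% | 4.8 | 18.4 |
| 20% | 9.6 | 30.7 |

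For example, at r = 5%: 1 − 0.95^4.586 = 0.210, and 0.210 × 48 = 10.1. The middle column is what a strict rule could remove from each arm by the primary endpoint. The last column is what it could remove from each active arm over the whole study. If every randomised participant is kept, all these exclusions are zero.

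**The case against.** The criterion sits in an eligibility list, and eligibility is settled before allocation. Screening staff can ask about planned travel, so the phrase may mean only that. Where the article intends removal after randomisation it says so, as it does for serious adverse events under Safety and adverse events. It has no such sentence for flights, and nothing says that a flyer's data are dropped. If a flight did end participation, data already collected could stay in the model and later values would be treated as missing at random. A condensed article may also leave the handling of travel after enrolment to a fuller document.

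Much of this stands. Deletion from the analysis is not stated, so the conflict becomes real harm only if someone applies the criterion to randomised participants. However, the planned-travel reading needs words that the criterion lacks, and criterion 5 shows how an entry-only rule is worded in the same list. Nor is this an omission left to another document: the article states a rule, and that rule collides with its own analysis principle.

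A reader might also infer that the rule falls far more heavily on the active arms in the primary comparison, given a window more than four times as long. The documents do not support that. The extra exposure begins after Week 7, and the three-arm model uses nothing later. The imbalance could enter only if a flight in follow-up erased a valid Week 7 score retroactively, and no section says so.

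**Conclusion.** The point holds as a conflict between the eligibility section and the analysis section. Criterion 10, as written, excludes randomised participants for a later event, and intention-to-treat does not allow that. How much harm follows depends on whether the rule is applied to randomised participants, which the article leaves open.

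The size cannot be derived from the documents. The counts in the second table rest on an assumed 7-week flight risk of 2% to 20%, a constant hazard, a last session at Week 6, and strict application of the rule. They show that the loss could be anywhere from trivial to substantial, and they are not an estimate. Within the three-arm comparison the windows are equal. Bias there from unequal windows would require retroactive removal, which is not stated. In the two-arm model to 6 months, the issue is loss of randomised participants from both arms.

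**What to change.** Reconcile Participants with Main analysis:
- Limit criterion 10 to facts known at entry: a trans-meridian flight in the past 3 months, or travel already planned. Remove the study period as a ground for exclusion after randomisation.
- State that all randomised participants, and all data collected from them, stay in the intention-to-treat analysis whether or not they fly.
- Record in-study flights by date in every arm.
- Add a sensitivity analysis that omits the sleep and circadian recordings affected by a flight. Keep assessments on their scheduled weeks.

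The cost is a short change to the eligibility and analysis text, a date field, and one sensitivity analysis. The downside is slight jet-lag noise in a few recordings. The protocol version is dated September 2023 and data collection was expected to end in December 2023, so rewording the entry criterion now changes little in recruitment. The main gain is that the analysis set is fixed before results are analysed. If anyone has already been excluded for a flight after randomisation, the report should give the number by arm and restore their collected data to the main analysis.
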